## Abstract

**Background:**

Exercise is crucial for individuals with paraplegia to reduce the risk of secondary diseases and improve independence and quality of life. However, numerous barriers such as inadequate accessibility restrict their participation in exercise programs. Digital exercise apps can help overcome these barriers. Personalization is considered a crucial feature of mobile exercise apps, as people with paraplegia have individual requirements regarding exercise programs depending on their level of impairment. Despite the increasing popularity of mobile exercise apps, there are none available that target the individual needs of this cohort. The ParaGym mobile exercise app prototype was designed to automatically tailor exercise sessions to the individual needs of users with paraplegia.

**Objective:**

This study aims to evaluate the feasibility, usability, safety, and preliminary effectiveness of the ParaGym mobile exercise app prototype.

**Methods:**

This pilot block-randomized controlled feasibility trial will include 45 adult participants with paraplegia. Eligible participants will be block randomized to either the intervention or waitlist control group. The intervention group will perform a 6-week exercise program using the ParaGym mobile exercise app, comprising three 35-minute exercise sessions per week. The waitlist control group will continue their usual care and receive access to the app after study completion. Participants will record all exercise sessions conducted with the app as well as additional exercise sessions conducted during the study period using exercise diaries. The primary outcomes include feasibility, usability, and safety. Feasibility will be assessed through semistructured interviews, study adherence, and retention rates. Usability will be measured using the System Usability Scale. Safety will be determined by the occurrence of adverse events. Secondary outcomes include the effects of the intervention on peak exercise capacity (VO_2_ peak); handgrip strength; independence, which will be measured using the Spinal Cord Independence Measure III (SCIM III); and health-related quality of life, which will be measured using the Short Form–36 Health Survey (SF-36).

**Results:**

Recruitment commenced in November 2022. Overall, 12 participants were enrolled at the time of submission. Data collection commenced in January 2023, with completion expected in April 2023.

**Conclusions:**

To the best of our knowledge, this is the first study to assess the feasibility, usability, and safety of an intelligent mobile exercise app for individuals with paraplegia. Thereafter, the app should be adapted according to the findings of this trial. Future trials with an updated version of the app should aim for a larger sample size, longer intervention duration, and more diverse target group. In the long term, a fully marketable version of the ParaGym app should be implemented. This would increase the access to personalized, independent, and evidence-based exercise training for this cohort and, in the future, other people who use wheelchairs.

**Trial Registration:**

German Clinical Trials Register DRKS00030370; https://drks.de/search/de/trial/DRKS00030370

**International Registered Report Identifier (IRRID):**

DERR1-10.2196/45652

## Introduction

### Background

A high level of sedentary behavior is associated with an increased risk of noncommunicable diseases, such as type 2 diabetes, cardiovascular diseases, and cancer [1]. This especially affects people who depend on a wheelchair for mobility, such as those with a spinal cord injury (SCI) [2,3]. Individuals with SCI show lower physical activity levels than able-bodied individuals and individuals with other chronic diseases [3,4]. This results in a 2- to 4-fold increased risk of obesity, diabetes, and cardiovascular diseases [5]. To prevent comorbidities and secondary diseases resulting from a sedentary lifestyle, exercise is of fundamental importance for this cohort [2,6,7]. Regular exercise increases muscle strength and cardiovascular fitness [8-13], leading to greater independence [10,14], improved mobility [8,14], and higher quality of life [11,15]. Furthermore, individuals with SCI who are engaged in sports show substantially higher social integration [15-17] and fewer depressive symptoms [10,17] than those in the inactive comparison group.

For individuals with SCI, engaging in sports is complicated by multiple infrastructural (eg, inadequate accessibility to buildings), internal (eg, not knowing how to exercise), and monetary barriers [18-20]. Digital exercise platforms have the potential to overcome these barriers and promote exercise participation because they do not require transportation, offer a guided program addressing the needs of individuals with SCI, and may be cheaper than a gym membership or personal training [21]. Using a digital exercise platform has been shown to promote adherence to exercise guidelines in able-bodied individuals during the COVID-19 pandemic, when access to sports facilities was restricted [22]. It can be assumed that this is also applicable to individuals with SCI. However, despite the wide variety [23] and recent increasing popularity of mobile fitness apps [24-26], a mobile exercise app targeting the needs of people with paraplegia does not exist.

Only 2 studies have assessed the feasibility of exercise apps for individuals with SCI, the WHEELS mobile health app [27] and the Fisiofriend app [28], although neither of these is available on the mobile app market. People with SCI have individual requirements regarding exercise programs depending on the level of impairment of their trunk stability and leg function [2,29]. Therefore, the exercise programs provided by apps must be personalized [30]. The exercise programs delivered by these 2 apps can be individualized by the users themselves [27] or by a clinician [28], but untrained individuals may not have the expertise to create and tailor their own exercise programs. In addition, the requirement of support from a health care professional further restricts the user’s independence.

To our knowledge, there is no mobile fitness app available that provides an exercise program for individuals with paraplegia that is automatically tailored to the user’s requirements while the user is completely independent of health care professionals. A prototype of the ParaGym mobile exercise app was developed to enable people with paraplegia to have their own virtual personal fitness coach in addition to their usual care. The app uses an intelligent algorithm that automatically personalizes its exercise program to the user’s needs, considering their physical capacity, fitness level, and exercise equipment.

Bizzarini et al [28] and Hoevenaars et al [27] showed that using a mobile app to promote physical activity in this cohort was feasible. However, there are no instances of conducting an exercise program tailored by an algorithm in this cohort. Therefore, a pilot study is needed to assess whether exercise using the new ParaGym mobile exercise app is feasible and safe for people with thoracic or lumbar SCI.

### Aims of the Study

The primary aims of this trial are as follows:

To qualitatively assess the feasibility of an app-based exercise program (ParaGym) tailored by an algorithm to the needs of people with paraplegiaTo investigate the usability of the ParaGym app prototype in terms of the app’s design, information provided by the app, app’s ease of use, satisfaction with the app, and app’s functionality using the System Usability Scale (SUS)To assess the safety of this program by considering adverse events (AEs) and serious AEs (SAEs)

The secondary aim is to analyze the effects of a 6-week training intervention using the ParaGym mobile exercise app on peak exercise capacity, handgrip strength, independence, and health-related quality of life.

## Methods

### Study Schedule

The SPIRIT (Standard Protocol Items: Recommendations for Interventional Trials) 2013 statement was used to develop the content, quality, and completeness of this protocol [31]. A SPIRIT study schedule (Table 1) and checklist (Multimedia Appendix 1) are provided.

**Table 1 table1:** SPIRIT (Standard Protocol Items: Recommendations for Interventional Trials) 2013 study schedule.

				Study period						
				Enrollment (t_0_)		Allocation (t_0_)		Postallocation period		Postintervention measure (t_1_)
**Enrollment**										
	Eligibility		✓							
	Informed consent		✓							
	Medical screening		✓							
	Allocation				✓					
**Intervention**										
	App						✓			
	Usual care						✓			
**Assessment**										
	**Participant characteristics**									
		Demographics			✓					
		Lesion level			✓					
		Lesion completeness			✓					
		Time since injury			✓					
		Anthropometrics			✓					
	**Feasibility**									
		Exercise diary					✓			
		Adherence					✓			
		Retention					✓		✓	
		Interview							✓	
	**Usability**									
		System Usability Scale							✓	
	**Safety**									
		Adverse events					✓			
		Serious adverse events					✓			
	**Effectiveness**									
		VO_2_ peak^a^			✓				✓	
		Maximal heart rate			✓				✓	
		Resting blood pressure			✓				✓	
		PO peak^b^			✓				✓	
		Borg RPE^c^			✓				✓	
		Handgrip strength			✓				✓	
		SCIM III^d^			✓				✓	
		SF-36^e^			✓				✓	

^a^VO_2_ peak: peak oxygen uptake.

^b^PO peak: peak power output.

^c^Borg RPE: Ratings of Perceived Exertion Scale.

^d^SCIM III: Spinal Cord Independence Measure III.

^e^SF-36: Short Form–36 Health Survey.

### Development of the ParaGym Mobile Exercise App Prototype

The development of the ParaGym mobile exercise app prototype is based on the Kernwerk mobile exercise app (Kernwerk GmbH), which was designed to improve general fitness in able-bodied individuals. The Kernwerk app offers daily functional training sessions created by exercise scientists and uses an intelligent algorithm to individualize these sessions to the user’s needs. The goal of the ParaGym project is to develop a prototype of an intelligent mobile exercise app for individuals with paraplegia.

The ParaGym mobile exercise app uses the same algorithm to provide an automatically individualized training program for people with paraplegia. The steps taken to develop the app are as follows. A user-centered approach was adopted to create the ParaGym exercise app for people with paraplegia. This included a survey among the target group and an extensive review of the literature [32] to identify both health-related and disability-related demands for an exercise program and a mobile fitness app. The results of the survey and the literature review revealed the following: (1) there is an urgent need for accessible and personalized exercise programs; (2) exercises with free weights are preferred over exercises with machines; (3) the exercise pool should contain stretching exercises and exercises to improve scapula coordination; (4) workouts should focus on the dorsal rather than the ventral shoulder musculature to avoid overuse injuries; and (5) users should be provided with comprehensive information about the potential risks of exercising (eg, increased risk of autonomic dysreflexia) and, if required, be cleared by a physician.

On the basis of the results of the survey and literature review, in cooperation with physiotherapists and sports scientists from different spinal cord centers, we developed a pool of 56 exercises to strengthen the core, upper, and lower body musculature; increase aerobic capacity; and improve wheelchair mobility and flexibility. Exercise videos and step-by-step descriptions were added for each exercise. Before integrating the exercises into the app, all exercises, including exercise videos and descriptions, were tested and evaluated in terms of feasibility, usability, and comprehensibility by 10 workshop participants with paraplegia [33]. Adjustments to all 3 components were made based on the feedback of the workshop participants and 3 physiotherapists. This resulted in a total of 67 exercises.

In the next step, further attributes were added for each exercise, specifying the required equipment (eg, dumbbells), required environmental conditions (eg, sufficient space for wheeling), difficulty level ranging from 1 (very easy, no specific requirements) to 150 (very difficult), and required physical capacity (eg, the extent of core stability and articular movements, such as “hip flexion” or knee extension). In addition, similar exercises were linked to each other. The linkage of the exercises and attributes results in an exercise scaling tree (Figure 1). All these factors are considered by the algorithm so that if 1 attribute does not apply, a similar but more appropriate exercise will be suggested automatically. Whereas information on available training equipment and environmental conditions is provided by the users, the appropriate difficulty level is assessed by rating each exercise on a scale from 1 (too easy) to 7 (too hard) after each training session (Figure 2D). If an exercise is rated “too easy,” a more advanced version of this exercise will be suggested to the user in the following training sessions. Thus, the intelligent algorithm can adjust the exercise level to the current fitness level of the user.

Training sessions focusing on different training goals (eg, improvement of wheelchair mobility or increase in strength) were created based on the exercise pool. The exercises and training sessions were then integrated into the mobile app.

**Figure 1 figure1:**
[figure not shown]
Example of an exercise scaling tree for the exercise “Superman hold.”

**Figure 2 figure2:**
[figure not shown]
Overview of the ParaGym mobile exercise app prototype. (A) Summary of the daily training session and home screen. (B) Exercise video and description. (C) Screen during workout mode showing the first exercise. (D) Difficulty level rating. (E) Exercise equipment settings. (F) Physical capacity settings.

### Description and Content of the ParaGym Mobile Exercise App Prototype

The ParaGym mobile exercise app prototype offers a daily training session that is automatically tailored to the individual requirements of people with paraplegia. Users must input information on their height, weight, age, gender, available exercise equipment (eg, dumbbells), and physical capacity (eg, impaired trunk stability and ability to extend the knee) when registering. The home screen of the app summarizes the daily training session (Figure 2A). Users can choose between different workouts by selecting another date on the timeline above the workout summary. Upon selecting one of the exercises within this summary, the exercise video and description will be displayed (Figure 2B). If one of the exercises selected for the workout is not appropriate, it can be excluded through the settings as described in the subsequent paragraph. To start a workout, users press “play.” Before starting the first exercise, users must confirm that they have read the general safety advice (eg, regarding bowel and bladder management) and specific advice regarding the execution of the exercise (eg, “sit up straight”). When starting the workout, a 10-second countdown will be shown before the first exercise appears on the display (Figure 2C). Users can skip to the next exercise by touching the screen. They can pause or discontinue the workout at any time.

On the home screen, users can tap on the hexagon symbol in the upper right corner to navigate to settings, where they can find a list of all exercises included. Upon selecting one of the exercises within the list, the users are given the option to block the exercise from being included in the workouts or view the exercise video and description. In addition, they can find a link to the project website, receive comprehensive safety information for exercising, and obtain contact information.

Users can make changes to their personal profile by selecting their name in the top row to access the profile settings. Within the section “Sportliches” (English: sporty), users can edit the information on their available exercise equipment (Figure 2E) and physical capacity (Figure 2F). Changes made to this information influence the exercise selection within the workouts.

### Study Design

This pilot mixed methods block-randomized controlled feasibility trial with an allocation ratio of 1:1 for the intervention and waitlist control groups is conducted at the German Sport University Cologne (GSU), Germany. The trial was registered with the German Clinical Trials Register (DRKS00030370).

Participants will be recruited at the GSU and the SCI center at the BG (*Berufsgenossenschaft*; English: occupational insurance association) clinic Tübingen, Germany. Participants will be recruited at the GSU via the project newsletter, the project website, social media, and by contacting rehabilitation centers and spinal cord associations. The BG clinic in Tübingen will recruit among their patients.

Measurements will be conducted at baseline (t_0_) and after the intervention (t_1_; Table 1). The primary outcomes (feasibility, usability, and safety) will be assessed during the intervention and at t_1_. The secondary outcomes (peak exercise capacity, handgrip strength, independence, and quality of life) will be assessed at t_0_ and t_1_. As data collection at the BG clinic Tübingen will focus on the primary outcomes and owing to limited capacity, the ramp exercise test for evaluating peak exercise capacity and handgrip strength test will be conducted only at the GSU and not at the BG clinic Tübingen. After randomization and group allocation, participants in the intervention group will be provided with the ParaGym mobile exercise app and uptake a 6-week home-based training intervention. The participants will be instructed to complete 3 training sessions per week. For this cohort, resistance training for at least 2 days a week is recommended [2,6]. As the training sessions delivered by the app comprise not only strength but also aerobic and flexibility exercises, we decided to provide training sessions for 3 days instead of 2. Eitivipart et al [34] recommend 3 sessions for a minimum duration of 20 minutes per week over at least 6 weeks to achieve substantial outcomes. The waitlist control group will proceed with their usual care and receive access to the mobile app once they have completed the trial. After the 6-week intervention, participants in the intervention group will be interviewed over the phone to assess feasibility and usability. Subsequently, both groups will return to the study site (t_1_) for the SUS questionnaire and secondary outcome measures. The study design and planned participant flow are presented in Figure 3.

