### Intervention

Following baseline measures, the intervention group will receive an introduction to the downloading process and a demonstration of the app [28,36-39]. They will also be provided with a user’s manual and 2 resistance bands with a resistance of their choice (TheraBand, The Hygenic Corporation), one of which is for backup. The intervention group will perform a 6-week home-based exercise program delivered by the ParaGym mobile exercise app, comprising three 35-minute exercise sessions per week. The app offers a different workout every day, and participants get to choose the days on which they want to exercise. An exercise session consists of 4 parts: warm-up, 2 exercise parts, and cooldown. The first exercise part focuses on the correct execution of the exercises at a moderate intensity and prepares the musculature for the high-intensity second part. Exercise sessions aim at various training goals, such as stabilization of the shoulder girdle and improvement of wheelchair mobility. The waitlist control group will only maintain usual care and receive access to the mobile app after postintervention measurements.

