### Measures

#### Primary Outcomes

##### Overview

The primary outcomes are feasibility, usability, and safety. Six weeks after commencing the intervention, semistructured interviews will be conducted via phone to investigate feasibility and usability. An interview guide was conceptualized based on interview domains and topics in similar studies [27,36,39-43]. The following topics will be addressed: (1) overall experience, (2) ease of use, (3) app functionality, (4) perceived safety, (5) technical functionality, (6) communication, (7) perceived effects and usefulness, (8) adherence and motivation, and (9) recommendation. The interviews will be audio recorded with the consent of the participants.

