##### Feasibility

During their first site visit, participants in both the intervention and waitlist control groups will be provided with an exercise diary (Multimedia Appendix 2). They will be asked to record the following: (1) any physical activities, including app exercise sessions, additional exercise sessions (eg, hand biking), and physical therapy; (2) the time spent performing the exercise; (3) the intensity of the exercise; and (4) any annotations concerning the exercise sessions as needed (eg, whether the session adapted by the algorithm was appropriate in terms of the choice of exercise and intensity). This will help obtain more information about the feasibility of the app in addition to the information provided in the retrospective interviews and help assess adherence to the program. Adherence rates in terms of completed sessions will also be measured based on app use data. Furthermore, retention rates will be measured by assessing dropout rates and reasons. As both adherence and retention are study outcomes, they should not be influenced by the investigators. Therefore, no measures will be taken to promote either of them. All outcome measures will be obtained regardless of adherence.

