##### Usability

The SUS [44] is a 10-item Likert scale ranging from 1 (“strongly disagree”) to 5 (“strongly agree”) and is a common tool for investigating the usability of health-related mobile apps [27,36,38,39,41-43,45,46]. The score will be converted according to Brooke [44], so the total score will range from 0 to 100. The app will be considered usable if the overall SUS score is at least 70 [47].

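### The SUS is assigned to both groups although controls have not had the app, it follows a usability interview, and it has no route for those who withdraw or miss t1

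*Protocol article*

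**What the plan says.** Usability is a primary outcome, measured by the SUS (range 0 to 100), with a fixed criterion in the Usability section: "The app will be considered usable if the overall SUS score is at least 70".

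- **Who completes it.** Study Design states that "both groups will return to the study site (t_1_) for the SUS questionnaire and secondary outcome measures". Table 1 places the SUS at t1 and names no group.
- **When controls get the app.** Study Design says that they "receive access to the mobile app once they have completed the trial". The Intervention section agrees: "The waitlist control group will only maintain usual care and receive access to the mobile app after postintervention measurements".
- **What comes before it.** Study Design says that after the 6 weeks "participants in the intervention group will be interviewed over the phone to assess feasibility and usability"; the t1 visit with the SUS comes after that. The Overview of the primary outcomes lists what the interview covers: "The following topics will be addressed: (1) overall experience, (2) ease of use, (3) app functionality", with six further topics.
- **Who is followed up.** The Feasibility section treats adherence and retention as outcomes, so "no measures will be taken to promote either of them". It adds that outcomes are collected whatever the level of adherence. Quantitative Analysis rules out imputation and accepts a retention rate of 75% or more as feasible.

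**The concern.** Three features of one measurement bear on a pass-or-fail criterion.

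First, taken literally, controls are asked to rate an app they have not used, and nothing in the article keeps their answers out of the overall score. The sentence on the interview names the intervention group; the sentence on the SUS names both groups.

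Second, participants discuss ease of use and functionality with an interviewer shortly before rating the same construct on a form.

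Third, the only scheduled SUS is at a site visit. Participants who leave the trial or miss the visit give no score. The article itself gives reasons why some might leave over usability. The Discussion foresees that prototype faults could affect feasibility and usability. The limitations add that a narrow choice of exercises may reduce motivation, especially in users with severe impairments, and that phones older than about 5 years may not run the app fully, whereas eligibility asks only for access to a smartphone.

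At stake is whether a score near 70 describes the people who were given the app.

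**Working it through.** **The plan's own figure.** Sample Size gives 30 participants at the GSU and 15 at the BG clinic: 30 + 15 = 45, as stated. There is no power calculation for the SUS, and the cut-off of 70 is a cited threshold, so there is nothing further to reproduce.

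**How many have used the app by t1.** With 1:1 allocation the GSU has 15 intervention and 15 control participants. The 15 BG participants are not randomized. That they all use the app is an assumption, since the article does not say so outright. App users are then 15 + 15 = 30, or 15 if only the GSU counts. At 75% retention this leaves 22.5 of 30 (about 23) or 11.25 of 15 (about 12).

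**If control answers were pooled.** Pooled mean = (users × user mean + 15 × control mean) / (users + 15). Assume that controls answer at the scale midpoint of 50 and users average 75:

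- 30 users: (30 × 75 + 15 × 50) / 45 = 66.7
- 15 users: (15 × 75 + 15 × 50) / 30 = 62.5

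To reach a pooled 70, users would need (70 × 45 − 15 × 50) / 30 = 80, or (70 × 30 − 15 × 50) / 15 = 90. Under this assumption pooling lowers the score.

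**If those lost differ from those measured.** Let r be retention and g the number of points by which those lost would have scored below those measured. The mean among those measured exceeds the mean over all app users by (1 − r) × g. The article gives no value for g, so a range is assumed:

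| Retention | g = 0 | g = 10 | g = 20 | g = 30 |
|---|---|---|---|---|
| 75% | 0 | 2.5 | 5 | 7.5 |
| 90% | 0 | 1 | 2 | 3 |

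At 75% retention and g = 20, an observed mean of exactly 70 corresponds to 70 − 0.25 × 20 = 65 over all app users.

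**Effect on the verdict.** Suppose that the mean over all app users is 67, 23 respond, and the criterion is applied to their mean. The expected observed mean is 67 + 0.25 × g, with standard error SD/√23. With an assumed SD of 15 this is 3.13, and the chance of observing 70 or more is:

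- g = 0: P(Z ≥ (70 − 67)/3.13) = 0.17
- g = 10: P(Z ≥ (70 − 69.5)/3.13) = 0.44
- g = 20: P(Z ≥ (70 − 72)/3.13) = 0.74

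From g = 0 to g = 20 the chance goes from 0.12 to 0.79 at SD 12, and from 0.24 to 0.68 at SD 20.

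**Order of interview and SUS.** No arithmetic applies. The topics overlap, but nothing in the article fixes the size or direction of any carry-over.

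**The case against.** A reader might infer that the usability verdict is drawn from the wrong people and is biased in the app's favour. The documents do not support that.

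- **Controls.** Nothing says that their scores enter the criterion. The sentence names two purposes for one visit and may be loose drafting: both groups return, and app users fill in the SUS. The participant flow figure, which might settle it, is not visible in the text at hand. If control scores did enter, they would more likely lower the result than raise it. What stands is a contradiction on the face of the text.
- **Non-users.** A reader might also infer that anyone who gives up on the app gives no score. The Feasibility section says otherwise: someone who stops using the app but stays in the trial is still measured. Only withdrawals and non-attenders are lost. Reasons for dropout are recorded, and retention has its own criterion, so such losses would be seen. They would still be missing from the score.
- **Upward bias.** It depends on those lost rating the app lower, which the article does not quantify. It is zero if dropout is unrelated to usability, and 25% loss is the most that the feasibility criterion accepts, not a forecast.
- **Interview.** The interviewer is not named and satisfaction is not a listed topic, so a claim of courtesy bias goes beyond the text. Airing problems first could lower the SUS. Reversing the order could in turn colour the interview.
- **Analysis details.** Handling of non-responders is commonly left to an analysis plan, and a rule against imputation does not forbid a sensitivity analysis. The article is therefore not at fault for leaving one out; it is proposed below as a safeguard.

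**Conclusion.** The point holds in a limited form. The statements on who completes the SUS, when controls get the app and which scores count towards 70 do not fit together and must be reconciled. Separately, the timing allows carry-over from the interview, of unknown direction, and the collection route leaves out those who withdraw or miss t1.

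Possible inflation from that loss runs from 0 to 7.5 points at the 75% retention limit, and from 0 to 3 points at 90%, for assumed gaps of 0 to 30 points. This matters if the true mean lies within a few points of 70, and little otherwise. That the result will be too favourable is not established. Because usability is a primary outcome judged against a fixed cut-off and the remedy is cheap, the change is worth making.

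**What to change.** 1. State that the SUS goes only to participants who were given the app, and base the criterion of 70 on them. Say whether this includes the BG participants, and name the summary statistic.
2. Have the form self-completed at the end of week 6, before the phone interview. If one must precede the other, the scored measure with the fixed cut-off is the one to protect.
3. Offer the 10-item form online, by mail or by phone to anyone who withdraws or does not attend t1. Such a reply should not count as retention, so the retention outcome is unaffected.
4. Report the number responding out of the number given the app, with a sensitivity analysis that gives non-responders lower scores over a stated range.

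The cost is a corrected sentence, a change in the order of two planned contacts and a little extra follow-up effort. The score may turn out less favourable. No extra visit is needed, and app use stays unprompted.
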